### Inclusion criteria

While previous studies have shown that there is a real benefit of peer education for people with very elevated HbA1c levels, we aim to include any person with type 2 diabetes. There are two main reasons for this decision. First, many *puskesmas* in Indonesia are currently not equipped to test HbA1c levels and would, hence, be unable to select patients based on their HbA1c levels. We, therefore, think that our intervention should reflect the reality of the current health system and investigate the suitability of measuring HbA1c levels for later implementation. Second, we suspect that there is also a benefit of joining peer education for those with better HbA1c levels, by helping them to prevent a worsening of the disease over time.

Therefore, we used the following inclusion criteria for patients in the peer education groups or the control groups:
Patients treated in *puskesmas* for type 2 diabetes in the intervention areaPatients who agreed to undergo the whole process of peer educationPatients who agreed to carry out all biological and survey assessments as required by the protocolPatients aged 20–79 yearsPatients not enrolled in another research program

The peer educators will need to fulfill the following requirements:
Can commit to attending 20 h of trainingAre willing to organize activities with other patients every monthHave basic diabetes self-management knowledge and supportive non-judgmental communication skillsWilling to leadLiterate

### Exclusion criteria

PregnancyBeing unable to physically attend peer education sessions

### Study procedures

The project has several phases. First, to inform the intervention design, qualitative interviews with nurses and diabetes patients were carried out. Then, for each *puskesmas*, patients with diabetes were recruited into the peer education program. An interview was carried out in each facility to receive the facility head’s consent to participate, to gather general information and information specific to diabetes treatment and, if possible, to obtain a list of diabetes patients. Additionally, health workers in the *puskesmas* and in the villages as well as patients who had already been interviewed were asked to suggest further people with diabetes who were associated with the relevant *puskesmas*.

At baseline, the patients recruited were interviewed by trained enumerators using a questionnaire. They were invited to the *puskesmas* on one predetermined day, during which the trained enumerators used point-of-care devices to test their HbA1c and lipid levels. The participants were informed of their test results. Blood was then drawn from the arm of participants by health-care professionals, which was used for laboratory as well as point-of-care tests of HbA1c and lipid profiles to determine the accuracy of the point-of-care test devices in the study setting under field conditions. In the middle and final assessments, only point-of-care tests using venous blood will be carried out.

In choosing potential peer educators, all participants were asked during the interviews if they would be interested in serving as a peer educator. Further, health facility staff were asked during the facility interview to suggest patients for this role. Out of the participants recruited, we determined potential peer educators based on three criteria: (1) their willingness to take on this role, (2) a recommendation from the health facility staff, and (3) how well they were already controlling their diabetes based on the HbA1c level from the baseline data.

Following data collection, the *puskesmas* were randomized. Because recruitment took place before randomization, the researchers, participants, and facility managers did not know which facilities would be allocated to the treatment and control groups. We used covariate-constrained randomization to ensure the treatment and control arms were balanced in terms of baseline covariates while maintaining the randomness of the allocation [20, 21]. The covariates took into account the composition of the group with regards to size of the group, and the age, sex, education, participation in other health programs,^3^ and diabetes control (mean HbA1c values) of the members, as well as the location of the *puskesmas* (rural or urban). Randomization was carried out using the statistics program Stata.

Peer education groups were formed at each *puskesmas* in the treatment group. Peer educators will receive continuous training in diabetes management skills and will be supported in the administrative processes (e.g., room booking) required to run their peer education group in their local sub-district.

To ensure that the effect of using peer education can be observed in comparison to normal patient education efforts, the control group will not receive any additional education apart from standard therapy.

As detailed in Fig. 1, 9 months after the first peer education session, a first follow-up will assess the implementation and the effects of peer education. The final assessment will take place 18 months after the first peer education session to assess the long-term effects of the intervention and the experience of participants.

We will then compare the outcomes between treatment and control groups, carry out a cost-effectiveness analysis, present the results to local health authorities, and discuss how to implement the program more widely if it proves to be effective.

### Economic evaluation

Costs related to the implementation of peer education will be collected from the the documented project expenditures. Data on resource use for diabetes treatment and care, including equipment, drugs, and doctor and hospital visits, will be collected retrospectively using cost information from the health insurance provider if possible, or via the expert opinion of local specialists. These data will be supplemented with information on participants’ health-care seeking behavior and utilization, drug use, and out-of-pocket payments collected through the surveys.

To estimate cost-effectiveness, the incremental cost-effectiveness ratio will be calculated from the health-care system perspective and the societal perspective taking into account out-of-pocket expenditures and costs related to participating in peer education. The incremental cost-effectiveness ratio is defined by the difference in costs between receiving no intervention plus standard diabetes care and the standard care plus intervention costs, divided by the difference in their effect. Here it represents the average incremental cost for peer education associated with one additional quality-adjusted life year.

### Data management

Data will be collected using tablets and directly entered into the electronic data entry program Open Data Kit (ODK collect). Data will be anonymized, and the original data will be stored separately on an encrypted hard storage device. Any biomarker data will be stored separately from the participant’s name on an encrypted hard storage device. The results of the biomarker tests will be reported back to the participants.

### Statistical methods

Random sampling and random assignment of intervention units to the treatment and control groups will allow us to interpret differences in mean outcomes as causal effects of the intervention. By comparing outcomes between participants in the peer education groups compared to study participants in the control group, we will be able to draw conclusions of the intent-to-treat effect and the size of the effect.

Because covariate-constrained randomization was used to balance the baseline characteristics, it is necessary to account for this design at the analysis stage [21, 22]. We will use general (generalized) linear mixed models to incorporate data structures that are both hierarchical and longitudinal and adjust for the covariates used during the covariate-constrained randomization [21, 22]. Standard errors will be clustered at the intervention unit level (*puskesmas*).

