### Number of participants and power calculation

The study aimed to include patients from all *puskesmas* in Banda Aceh and Aceh Besar.^2^ Power calculations indicated that with 680 participants in 34 clusters, an assumed intra-cluster correlation of HbA1c of 0.37, and a pooled standard deviation of HbA1c of 1.25, we would have 80% power to detect a difference of 0.5 in mean HbA1c using a significance level of *p* = 0.05 and 90% power to detect a difference of 0.686 using a significance level of *p* = 0.01. We chose a difference of 0.5 in mean HbA1c, as this has been determined as a clinically meaningful threshold [19]. At the end of the recruitment phase, we had been able to recruit 534 participants from 31 *puskesmas*. However, two *puskesmas* could not be used as separate cluster units since their low recruitment numbers prevented the formation of a peer education group. We decided to assign the participants from these *puskesmas* to the geographically closest *puskesmas*. This reduced the number of clusters from 31 to 29, which gives 80% power to detect a difference of 0.57 in mean HbA1c using a significance level of *p* = 0.05 and 90% power to detect a difference of 0.78 using a significance level of *p* = 0.01.

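### Clustered standard errors with 29 clusters and seven adjustment covariates, with no small-sample correction named, can make the primary test anti-conservative (about 5–13% against a nominal 5%, depending on choices left open)

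*Protocol article*

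**What the plan says.** The Statistical methods section names general or generalised linear mixed models for hierarchical, longitudinal data. They are to "adjust for the covariates used during the covariate-constrained randomization". It closes with the variance rule: "Standard errors will be clustered at the intervention unit level", the unit being the puskesmas. It names no form of sandwich estimator, small-sample correction or reference distribution.

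The Study procedures section lists the covariates as features of group composition: group size, age, sex, education, participation in other health programmes, "diabetes control (mean HbA1c values) of the members", and rural or urban location. That makes seven.

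The section on number of participants and power reports that "we had been able to recruit 534 participants from 31" puskesmas. Two of these were merged into neighbours: "This reduced the number of clusters from 31 to 29". The Study design section assigns half of the clusters to peer education, which implies about 14 against 15. The Outcome measures section defines the primary outcome as change in HbA1c from baseline to the final assessment, with a midline measurement between.

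**The concern.** The sandwich variance is justified for a large number of clusters. With few, it is biased downwards because residuals are smaller than the errors they stand in for. Each covariate that varies only between clusters makes this worse. A normal reference, or a t reference with 28 df that ignores the covariates, adds to the problem.

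At stake are the p-value and confidence interval for the effect on HbA1c. The article ties two decisions to the programme proving effective: setting up groups in the control clusters, and discussing wider implementation with the health authorities. The same standard-error rule is written for every outcome, so the secondary results share the weakness.

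**Working it through.** **Inputs from the article.** 29 clusters, 534 participants (534/29 = 18.4 per cluster), seven covariates, ICC 0.37, SD 1.25.

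**Assumed, because not stated.** A 14/15 split, cluster-size coefficient of variation about 0.35 (where set), two-sided tests, and allocation drawn from the best-balanced 10% of sampled allocations. Some runs also used lower ICCs, down to 0.037.

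**The plan's own figures.** The article states no type I error, so there is none to reproduce. Its only related figures are detectable differences at 80% power: 0.5 for 680 participants in 34 clusters and 0.57 for 534 in 29. With DE = 1 + (m − 1) × ICC and difference = (1.96 + 0.842) × SD × √(2 × DE/(N/2)):

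- 680/34: DE = 1 + 19 × 0.37 = 8.03; difference = 2.802 × 1.25 × √(16.06/340) = 0.76.
- 534/29: DE = 1 + 17.41 × 0.37 = 7.44; difference = 2.802 × 1.25 × √(14.89/267) = 0.83.

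Neither stated figure is reproduced. That is a separate matter, and the present point does not depend on it.

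**Approximate size of the bias, seven cluster-level covariates.** Intercept, arm and seven covariates make 9 parameters, leaving 29 − 9 = 20 between-cluster df. The uncorrected variance is about 20/29 = 0.69 of the true value, so the standard error is about √0.69 = 0.83 of what it should be, or 17% too small. Treating the correctly scaled statistic as t with 20 df:

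- Uncorrected, normal reference: effective cut-off 1.96 × √(20/29) = 1.628; rejection 11.9%.
- Scaled by G/(G − 1), where G is the number of clusters, normal reference: 1.96 × √(20/28) = 1.657; rejection 11.3%.
- Scaled by G/(G − 1), t with 28 df: 2.048 × √(20/28) = 1.731; rejection 9.9%.

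**Simulation under no effect, nominal 5%.** The ranges span uncorrected and G/(G − 1)-scaled sandwich errors, with normal or t(28) reference.

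| Analysis | Rejection rate |
|---|---|
| Final value, all seven covariates as cluster summaries | 9.6–13.4% |
| Final value, five as patient values and two (size, location) at cluster level | 6.1–8.8% |
| Three waves, arm-by-time contrast, all seven as cluster-level main effects | 4.9–7.4% |

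Within the last row: 6.4–7.4% uncorrected, 6.0–6.6% with G/(G − 1) and a normal reference, and 4.9–5.9% with G/(G − 1) and t(28). That row used 3,000 runs per setting, so the Monte Carlo margin near 5% is 1.96 × √(0.05 × 0.95/3000) = 0.8 percentage points. Its lower end cannot be told from nominal. It also assumes that 20% or 50% of the cluster variance changes from wave to wave.

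**After correction, in the least favourable case (first row).** Model-based standard error with t(20): 4.7–5.4%. CR2-type sandwich with t(20): 5.2–5.8%. CR2 with Satterthwaite df: 4.5–5.1%.

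**The case against.** A reader might infer that the plan adopts ordinary, uncorrected sandwich errors with seven cluster-level terms, and so roughly doubles the type I error. The document does not support this, for three reasons.

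- The sentence on clustered errors is compatible with a corrected form such as CR2. The variant and the df are details that an article may leave to a fuller plan.
- The balancing covariates are described as group composition, but the analysis section does not say whether age, sex, education, programme participation and HbA1c enter the model as puskesmas means or as patient values.
- The primary outcome is a change, and the model is longitudinal. If the effect is an arm-by-time contrast, covariates entered as main effects take almost nothing from it, and the argument from 20 df largely falls away.

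All three objections stand as limits on size. They do not remove the point. The article does fix a variance rule, and it fixes that rule without the qualification needed at 29 clusters. Standard forms of the rule exceed 5% in nearly every setting examined; only the longitudinal contrast with a t(28) reference comes close to nominal.

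**Conclusion.** The point holds conditionally. A standard clustered standard error, uncorrected or scaled only by G/(G − 1), is anti-conservative here. The inflation is about 10–13% in the least favourable reading, 6–9% with patient-level covariates, and 5–7% for the three-wave contrast. Doubling requires three unstated choices to coincide: a final-value analysis, all seven covariates at cluster level, and no adequate small-sample correction.

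The figures come from simplified simulations. The re-checks of the first two cases include runs with the ICC treated as known and a single follow-up; the three-wave runs treated the variance components as known. The direction is firm and the exact size is not. An unseen analysis plan may already name a correction. The point is a cheap improvement to make before the final data are analysed.

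**What to change.** Replace the sentence on clustered standard errors with a rule along these lines: the arm effect is tested with the mixed model's own standard error and Kenward-Roger or Satterthwaite (between-cluster) degrees of freedom; if robust errors are kept, they are CR2 bias-reduced with Satterthwaite degrees of freedom; the clusters are the 29 randomised units, with the two merged puskesmas counted within the units they joined. State as well whether each covariate enters as a cluster summary or a patient value, and whether the primary effect is a final-value or an arm-by-time contrast. Optionally, confirm the result with a permutation test restricted to the allocations that were eligible under the constrained randomisation.

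The cost is one sentence and a software option, with no new data. Intervals widen by about 20–28% in the least favourable case (2.086/1.731 = 1.20 to 2.086/1.628 = 1.28, where 2.086 is the t(20) quantile), and by less where the inflation is smaller.

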### Data monitoring

Because this study does not involve any testing of medications or procedures that are outside the usual care provided to individuals with type 2 diabetes, monitoring patient safety will be limited to mandatory reporting of adverse events and unanticipated problems. Participants will be made aware of unexpected test findings identified during the trial. Adverse events include clinical reactions to blood draws related to the study, as well as any reported stigma or physical or mental harm as a result of participation in the study, including disclosure of diabetes status.

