### Use of peer education

Depending on the number of patients recruited per *puskesmas* and the number of potential peer educators, one or two peer educators will be selected per *puskesmas*, to limit the group size to 13 participants. Peer education sessions are planned to be held once a month for 18 months. They will be conducted by the peer educator only, without the presence of a trained nurse or a member of the research staff, to avoid any potential changes in the behavior of the peer educator or the patients. To preserve some flexibility in how peer educators conduct the peer education sessions and react to the needs of the group, we will refrain from closely monitoring each session. Rather, we will use feedback from the peer educators about the sessions to determine if they are successful in discussing the planned topics.

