### Foreseeable risks, discomforts, and inconvenience to participants

Trial participation is voluntary, so that participants may leave the trial at any time for whatever reason. Because the provision of education should only add to the participants’ knowledge about how to manage their diabetes, we see no immediate risks for participants. This additional information may lead to an increased awareness of the risks of sustained high glucose levels and could increase anxiety in participants. Theoretically, the personal experience or beliefs of the peer educators may lead them to diverge from the educational material to promote potentially harmful or ineffective practices for treating diabetes.

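### Harm is counted passively and by attribution to the study, so counts are not like-for-like between arms, and the educator-related risk the protocol names has no stated direct, arm-neutral detection route

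*Protocol article*

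**What the plan says.** Under Data monitoring, the protocol article states that "monitoring patient safety will be limited to mandatory reporting of adverse events and unanticipated problems". It then describes the events: "Adverse events include clinical reactions to blood draws related to the study", together with stigma that is reported and reported "physical or mental harm as a result of participation in the study".

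Under Foreseeable risks, the article names two ways the intervention could do harm. Greater awareness of risk "could increase anxiety in participants", and the educators' own experience or beliefs "may lead them to diverge from the educational material to promote potentially harmful or ineffective practices for treating diabetes". The Background adds that traditional beliefs and alternative medicines are still fairly common in the setting.

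Under Use of peer education, sessions run with no nurse or research staff in the room and are deliberately not closely monitored. Instead, "we will use feedback from the peer educators about the sessions to determine if they are successful in discussing the planned topics".

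Provisions in place to minimize risk answers the educator risk with careful selection, insistence on the materials and possibly some myth-correcting content. Study design states that allocation is open to participants, managers and investigators once clusters are randomized.

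**The concern.** A harm count supports a comparison only if an event has the same chance of being recorded in either arm. Here the described harm category needs two things: someone must report the event, and it must be put down to taking part. A participant who follows a trusted peer's advice on a remedy may not connect a later problem with the study. A control participant has no sessions to connect anything with. Whoever judges the link knows the arm. The resulting counts could differ, or agree, for reasons unrelated to the true amount of harm.

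The named educator risk adds a second difficulty. The person who might stray from the material is also the main stated source on what happened in the session, and the question put to that person is whether planned topics were discussed, not whether other advice was given. At stake is whether the trial can say anything direct about harm when it informs a decision on wider roll-out, and whether a null HbA1c result can be told apart from sessions that were missed or off-message.

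**Working it through.** The article gives no harm rate and no safety threshold, so there is no stated figure to reproduce. The check sets the sections side by side and then sizes the dilution.

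**Step 1. Detection route for the named risk.**
- *Risk* (Foreseeable risks): educators "diverge from the educational material to promote potentially harmful or ineffective practices for treating diabetes".
- *Prevention* (Provisions in place to minimize risk): selection, instruction, possible myth correction. No detection step is stated.
- *Observation* (Use of peer education): no staff present; educator feedback on topic coverage.
- *Event reporting* (Data monitoring): harm reported and resulting from participation. Unanticipated problems are also reportable, but this risk is one the article already anticipates.
- *Both-arm data* (Outcome measures, Economic evaluation, Statistical methods): HbA1c, MARS-5 adherence, Diabetes Distress Scale, and surveyed drug use and health-care use, with outcomes compared by intention to treat. These exist, but none is labelled a safety outcome.

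The only arm-neutral route is therefore the last, and it is indirect.

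**Step 2. How diluted is that route?** Inputs: 534 participants and a stated detectable difference of 0.57 at 80% power (Number of participants and power calculation); groups limited to 13 (Use of peer education). Assumptions: equal arms, so 534 / 2 = 267; one educator deviates; HbA1c rises by 1 to 3 percentage points in every member of that group.
- Share of the arm affected: 13 / 267 = 4.9%.
- Shift in arm mean: 13 / 267 × 1 = 0.05, to 13 / 267 × 3 = 0.15.
- Compared with 0.57, that is about 9% to 26% of the stated detectable difference.

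**Step 3. How many groups would have to deviate to move the mean by 0.57?**
- At 3 points each: 0.57 × 267 / 3 = 51 participants, about 4 groups of 13.
- At 1 point each: 0.57 × 267 / 1 = 152 participants, about 12 groups.
- An arm of 267 needs at least 267 / 13 = 20.5, so 21 groups.

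Isolated deviation would be lost in the mean; widespread deviation could show, although the mean is a net figure and benefit in other groups would offset it. The 0.57 is used as stated.

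**Step 4. Precision of a direct item.** Assume 5% in each arm answer yes to an item. The half-width of the 95% interval for the difference is 1.96 × sqrt(2 × 0.05 × 0.95 / 267 × DE), with DE = 1 + (534/29 − 1) × ICC = 1 + 17.4 × ICC.
- ICC 0: DE = 1, half-width 3.7 percentage points.
- ICC 0.05: DE = 1.87, half-width 5.1 points.
- ICC 0.37 (the article's value for HbA1c, borrowed here): DE = 7.4, half-width 10.1 points.

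Direct items give a like-for-like comparison, but not a precise one for uncommon events.

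**The case against.** The strongest reply is that the consequences of bad advice are measured. If participants stop or replace treatment, MARS-5 and the surveyed drug use should register it; worsening control should appear in HbA1c; the distress scale bears on the anxiety risk; health-care use is surveyed. All of this is collected in both arms. That stands, and it rules out a reading someone might take from the safety section alone: that such harm cannot be seen or compared between arms, or that no outcome could show it. What remains is that these measures are taken only at 9 and 18 months, do not give a reason for stopping medication, do not identify an acute low blood sugar episode, and dilute a single deviating group as shown.

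Nor is the reporting route strictly closed. The event description opens with a word that leaves room for other events, and Study procedures plans to assess implementation at 9 months and participants' experience at 18 months. So the educator is the main stated source on sessions, not provably the only one. The article does not say, however, that those assessments cover session content or advice on remedies.

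Leaving sessions unobserved is a reasoned choice, made to avoid altering behaviour and to keep flexibility. It is not criticised here, and the fix does not touch it.

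Finally, this is a condensed article, and the questionnaires may already hold some of the items proposed. For that reason the point rests on what is stated: monitoring limited to reported events, harm described by its link to participation, and educator feedback used to judge sessions.

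**Conclusion.** The concern holds in a limited form. As written, harm ascertainment is passive and depends on attribution, in a trial open after allocation whose controls attend no sessions, so harm counts are not like-for-like between arms. The educator risk has prevention but no stated direct, arm-neutral means of detection. It would surface only indirectly and diluted: a shift of 0.05 to 0.15 in mean HbA1c if one group of 13 worsened by 1 to 3 percentage points, against a stated detectable difference of 0.57. Those figures assume equal arms and an invented rise; the argument about attribution does not depend on them.

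A reader might go further and expect an empty harm table whatever happened, or conclude that a null HbA1c result could never be traced to poor delivery. The article supports neither, given the both-arm outcomes and the planned assessment of implementation and experience. The primary analysis is unaffected. This is a change worth making, not a flaw that undermines the trial.

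**What to change.** 1. At the 9- and 18-month interviews, ask both arms the same fixed items whatever the perceived cause: episodes of low blood sugar, hospital admission, and stopping or replacing prescribed diabetes treatment. Where the questionnaire already has an item, keep it and only add the reporting.
2. Designate these as safety outcomes and report them by arm beside the existing adherence, drug-use and health-care-use data, with intervals that allow for clustering by *puskesmas*.
3. In the intervention arm, within the implementation and experience assessments already planned, ask participants how many sessions they attended and whether they were given any advice on medicines or remedies, so that delivery is not judged from educator feedback alone.
4. Keep the current reporting of study-related events alongside, and state that it is not used to compare arms.

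The cost is a few more interview minutes and one more table, with no extra staff or procedures and no observer in sessions. Both follow-ups (April 2020 and January 2021) fall after the date of protocol version 1.5 (5 August 2019). The limitation is low precision for rare events, which should be stated with the results.
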